### Statistical Analysis of Primary and Secondary Endpoints

Data will be presented as counts (percentages) and mean ± SEM as appropriate and will be analyzed using parametric or non-parametric tests. The primary functional endpoint will be assessed as difference in proportions and the relative risk between groups will be estimated with exact 95% confidence intervals and *P*-values. The proportion of patients with primary functional clinical endpoint and other binary outcomes will be analyzed using the same methods, and time to events within 12 months will be compared between groups using log-rank tests. A multivariable stepwise linear regression (*p* < 0.2 to enter, *p* < 0.1 to stay) analysis will be used. Covariates will include age, sex, diabetes, smoking, renal function, previous myocardial infarction, type of acute coronary syndrome presentation, body mass index, vessel(s) involved. The grouping factor (QFR vs. angiography) will be forced into the model. A *p*-value <0.05 (2-sided) will be considered statistically significant. All secondary endpoints will be analyzed by descriptive statistics and appropriate exploratory *p*-values.

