### Study Procedures

#### Consent and Randomization

Patients will be contacted after successful interventional treatment of the ACS, which includes treatment of all culprit lesions (typically >90% diameter stenosis or thrombotic lesions) and guideline-directed medical therapy. If all inclusion and no exclusion criteria are met, consent will be obtained. Prior to randomization, QFR will be measured in all participants in all coronary arteries presenting a lesion with 30–90% diameter stenosis. Patients with vessels with residual QFR <0.80 (residual QFR is the QFR calculated in the absence of the target lesion. A QFR <0.80 assumes that treatment of this/these focal lesion(s) would not remove the source of ischemia, such as in the case of diffuse disease) will be excluded. Thereafter, randomization will be performed in a 1:1 ratio with the use of randomly permuted blocks of 2, 4 or 6. The participants and treating physicians will be blinded to the treatment group allocation. Patients will be randomized to one of two strategies: angiography-guided (reference) or QFR-guided revascularization (experimental). In the reference arm, any decision regarding the treatment of non-culprit lesions will be based on the angiography performed at the time of the index PCI and the physicians will be kept blinded to the outcomes of QFR analysis. This strategy reflects the typical procedures used in daily routine; all lesions believed to be significant at angiography will be treated in one staged session. In patients randomized to QFR-guided revascularization, all lesions (one or more per vessel) associated with a vessel QFR <0.80 and a residual QFR >0.80 will be treated in one staged session (13). The treatment plan will be scheduled (according to angiography or QFR) by study investigators not involved in patient care. Only experienced medical staff, certified to use the software with the QFR system, will perform the measurements. Analyses will be conducted with QAngio XA 3D from Medis Medical Imaging Systems BV (Leiden, the Netherlands).

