### Study Endpoints

*Primary endpoint (functional): the primary endpoint (functional) is* the proportion of patients assigned to medical treatment in the two groups (QFR vs. Reference) (see Table 2).

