### Power Calculation

Functional endpoint: For the sample size calculation, the results of the FLOWER-MI trial will be used. In this study, which enrolled multivessel disease patients with at least one non-culprit lesion >50%, PCI was performed in 388 of 586 patients (66.2%) in the FFR-guided group and in 560 of 577 patients (97.1%) in the angiography-guided group; 366 of 826 (44.3%) lesions in the FFR group were reclassified from angiographically significant to non-significant based on FFR. Of note, although we allow patients with lesions >30% in our study, we foresee that [based on the results of the FLOWER-MI (10)], about 97% of the participants in our study will have at least one lesion >50%. Conservatively, we hypothesize a rate of decision to not perform PCI in our angiography group 4 times higher than that observed in the FLOWER-MI study (i.e., 13%). In the QFR group, we hypothesize a conservative decision in 33% (similar to that observed in the FLOWER-MI study). Based on this hypothesis, 176 patients are required to have a 90% chance of detecting, as significant at the 5% level, a decrease in the primary outcome measure from 33% in the QFR group to 13% in the angiography group.

Clinical endpoint: The clinical endpoint combines hard endpoints and angina: in the FORZA trial, comparing a FFR-guided with a OCT-guided PCI strategy, a composite of MACE + significant angina (all-cause death, non-fatal myocardial infarction, target vessel revascularization, SAQ <90) was taken. The incidence of this endpoint was 14.8% at 1 year in the FFR group (23). The incidence of the same endpoint in the FAME trial was 32.4% at 1 year in the angiography group (3). Given these assumptions, 176 patients are required for a power of 80% and an alpha error of 5% to observe a difference assuming an incidence of 14.8% in the QFR group and 32.4% in the angiography group.

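### The functional primary endpoint is compared as raw proportions, although the pre-randomisation QFR class, known in both arms, could tighten the estimate at no data cost

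*Protocol article*

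**What the plan says.** The functional primary endpoint (Study Endpoints) is the share of patients in each group who are assigned to medical treatment rather than PCI. For its analysis, Statistical Analysis of Primary and Secondary Endpoints states: "The primary functional endpoint will be assessed as difference in proportions and the relative risk between groups", with exact 95% confidence intervals and P-values. No adjustment is mentioned for this comparison.

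Consent and Randomization states: "Prior to randomization, QFR will be measured in all participants in all coronary arteries presenting a lesion with 30–90% diameter stenosis". Patients with a vessel whose residual QFR is below 0.80 are excluded at that step. In the QFR arm, lesions "associated with a vessel QFR <0.80 and a residual QFR >0.80 will be treated in one staged session". In the reference arm the decision rests on angiography, and "the physicians will be kept blinded to the outcomes of QFR analysis".

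Power Calculation assumes medical-treatment rates "from 33% in the QFR group to 13% in the angiography group" and concludes that "176 patients are required to have a 90% chance of detecting, as significant at the 5% level". The Hypothesis section plans 100 patients per group.

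**The concern.** The endpoint is assignment, not treatment received. Once the low-residual-QFR patients are excluded, assignment in the QFR arm follows from one baseline fact: whether any vessel has a QFR below 0.80. The same fact is recorded for every reference-arm patient before randomisation, so those patients also show what the QFR rule would have assigned. A raw comparison ignores this. It estimates the QFR-arm proportion from about 100 patients when about 200 carry the information.

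At stake is the width of the interval, and some power, for the first of the two primary endpoints. No new measurement would be needed.

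**Working it through.** **Inputs.** Medical-treatment rates p1 = 0.33 (QFR) and p0 = 0.13 (angiography), 90% power and N = 176 (Power Calculation); two-sided 5% (Statistical Analysis of Primary and Secondary Endpoints); 1:1 allocation (Consent and Randomization); 100 per group (Hypothesis).

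**Step 1: the plan's own figure.** With unpooled variance, n per arm = (1.960 + 1.282)² × [0.33 × 0.67 + 0.13 × 0.87] / 0.20² = 10.507 × (0.2211 + 0.1131) / 0.04 = 87.8. This rounds up to 88 per arm, or 176 in total, so the stated figure reproduces.

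**Step 2: the raw analysis at 100 per arm.** SE = √(0.3342 / 100) = 0.0578. Normal-approximation power = Φ(0.20/0.0578 − 1.96) = Φ(1.50), about 93%. Exact enumeration gives 93.1% for chi-square and 90.4% for Fisher's test.

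**Step 3: standardising over QFR class, simplest case.** Suppose the angiographic decision is independent of QFR class. The QFR-arm proportion can then be estimated from both arms, which halves its variance term. Variance × n per arm falls from 0.2211 + 0.1131 = 0.3342 to 0.1106 + 0.1131 = 0.2237. The ratio is 0.669: 33% less variance and, since √0.669 = 0.818, an SE 18% smaller. At 100 per arm the SE is √(0.2237/100) = 0.0473. The N needed for 90% power would fall from 176 to about 118.

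**Step 4: range over the unknown agreement.** Let a be the probability that angiography assigns medical treatment when the QFR rule would also do so, and b the probability when the QFR rule would treat, so b = (0.13 − 0.33a)/0.67. Then

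N × variance = 0.2211 × (1 − a + b)² + 2 × [0.33a(1 − a) + 0.67b(1 − b)],

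against 2 × 0.3342 = 0.6684 unadjusted. The documents give no value for a, so it is varied. The last column is the normal approximation.

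| Agreement (assumed) | a | b | N × variance | Variance cut | SE cut | Variance cut, log RR | Power, 100 per arm |
|---|---|---|---|---|---|---|---|
| Maximum disagreement (implausible) | 0 | 0.194 | 0.5248 | 21% | 11% | 3% | 97% |
| Independence | 0.13 | 0.13 | 0.4473 | 33% | 18% | 12% | 99% |
| Some agreement | 0.20 | 0.096 | 0.3987 | 40% | 23% | 19% | 99% |
| Stronger agreement | 0.30 | 0.046 | 0.3209 | 52% | 31% | 32% | >99% |
| Full nesting (maximum) | 0.394 | 0 | 0.2388 | 64% | 40% | 47% | >99% |

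**Step 5: simulation.** With 100 per arm and 20,000 runs per setting, covariate adjustment for QFR class cut the variance by 32% at independence, 51% at a = 0.30 and 64% at full nesting. A separate simulation of the standardised difference gave power of 98% at independence, 96% at maximum disagreement and 100% at full nesting. I use these slightly lower power figures in the conclusion.

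**Step 6: relative risk.** At independence, variance × n of the log relative risk falls from 0.67/0.33 + 0.87/0.13 = 2.03 + 6.69 = 8.72 to 1.02 + 6.69 = 7.71, a cut of 12%. The gain is smaller because the rarer reference-arm outcome dominates on this scale.

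**Step 7: form of the covariate.** A linear term in continuous QFR, with normality assumed, would recover only about 20% of variance at independence. The full gain needs the class that the treatment rule uses.

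**The case against.** The strongest objection is that nothing here is invalid. A raw difference between randomised arms is unbiased and keeps its error rate, and at the planned 100 per arm even the exact test reaches the 90% target. That stands. It limits the point to one of efficiency.

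Several stronger readings are tempting, and the documents do not support them:

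- **That the endpoint is underpowered.** Exact-test power would be 86% at 88 per arm, but the plan is to recruit 100 per arm, and the protocol gives no loss rate that would bring 200 down to 176.
- **That a third of the precision is lost outright.** The third is variance of the risk difference under assumed independence. It is 18% in SE, and about 12% of variance for the relative risk that the plan also reports. Positive agreement between the two decisions would make the gain larger.
- **That chance imbalance in QFR class is a second harm.** At 100 per arm that imbalance has an SD of √(2 × 0.2211/100), about 6.6 percentage points. The unadjusted SE already covers it, so this is the same precision point restated.
- **That QFR was wrongly left off the covariate list.** The list ("Covariates will include age, sex, diabetes, smoking, renal function, previous myocardial infarction, type of acute coronary syndrome presentation, body mass index, vessel(s) involved") belongs to a stepwise linear regression with no stated outcome. Nothing ties it to this binary endpoint, so the omission shows little.

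A fair practical objection is that a raw difference with exact inference is transparent and available in MedCalc and SPSS, the software named under Statistics, whereas a standardised estimate needs some code.

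**Conclusion.** The point holds as a low-cost improvement in efficiency, not as an error in validity or power. The protocol collects before randomisation, in both arms, the variable that essentially determines the functional endpoint in one arm, and then fixes an analysis that does not use it. With 33% versus 13%, standardising over QFR class would cut the variance of the risk difference by about 33% at independence (range 21% to 64%). Power at 100 per arm would rise from about 93% (chi-square) or 90% (exact) to about 98% (range 96% to 100%).

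This rests on three assumptions: the planning rates are right, QFR-arm assignment follows the stated rule, and the agreement between the angiographic decision and QFR class lies in the range shown. The second is not critical: with 5% random departure from the rule at 88 per arm, simulated power was 94% (chi-square), 91% (Fisher) and 98% (standardised), the true difference then being 0.217.

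**What to change.** In Statistical Analysis of Primary and Secondary Endpoints, make the primary functional analysis the marginal risk difference, with the relative risk, standardised over pre-randomisation QFR class (any vessel QFR <0.80, yes or no). Specify the following:

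- **Estimate:** proportions in each arm-by-class cell, weighted by the class distribution of the analysed population with both arms combined. The weights must match the analysis set, because Statistics makes the modified intention-to-treat population primary. Use cell proportions rather than a logistic model, since class predicts the outcome perfectly in the QFR arm.
- **P-value:** a re-randomisation test of the standardised difference. A plain Wald test ran at 5.2% to 6.0% under the null in simulation.
- **95% confidence interval:** a named method, such as a stratified bootstrap or an influence-function variance.
- **Support:** the raw difference with its exact interval.

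The cost is one paragraph of text and a few lines of code beyond the standard menus of the named software. The downside is that the closed-form exact interval becomes a supporting result. No extra data are needed.

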#### SAQ Questionnaires

The first SAQ questionnaire will be administered before the staged revascularization, i.e., ~4 weeks after the ACS event. The SAQ-7 provides a quantitative analysis of 5 domains (physical limitation, angina stability, frequency, treatment satisfaction, and quality of life) reflecting the impact of angina on patients' health status during the previous 4 weeks. Scores for each domain go from 0 to 100, with 100 defining absence of limitations. The SAQ score at 1 month after ACS correlates with the subsequent incidence of mortality, hospitalization, and resource use (22). The SAQ-7, along with clinical follow-up data (death, re-hospitalization, re-intervention) will be collected at 3 and 12 months after protocol-mandated complete revascularization during office or telephone visits.

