### Hypothesis

A = Change in the SAQSS after 3 months to baseline with QFR-guided treatment

B = Change in the SAQSS after 3 months to baseline with reference treatment

Hypotheses: H0: A = B; H1: A ≠ B (Overall type I error rate = 5% (two-sided) with a power = 90%).

Based on these assumptions, the sample size is 178. We plan to recruit 100 patients per group.

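### The stepwise linear regression names no outcome and leaves out baseline SAQ; a fixed-covariate ANCOVA would make the SAQ comparison more precise at almost no cost

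*Protocol article*

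**What the plan says.** All references are to the protocol article.

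- **Adjusted model** (Statistical Analysis of Primary and Secondary Endpoints): "A multivariable stepwise linear regression", with p<0.2 to enter and p<0.1 to stay. The dependent variable is not named. The candidates are: "Covariates will include age, sex, diabetes, smoking, renal function, previous myocardial infarction, type of acute coronary syndrome presentation, body mass index, vessel(s) involved". Treatment is protected from selection: "The grouping factor (QFR vs. angiography) will be forced into the model".
- **Binary endpoints** (same section): "The primary functional endpoint will be assessed as difference in proportions and the relative risk between groups", with exact confidence intervals. The clinical primary is placed under the same rule: "other binary outcomes will be analyzed using the same methods, and time to events within 12 months will be compared between groups using log-rank tests". Secondary endpoints get descriptive statistics and exploratory p-values.
- **SAQ timing** (SAQ Questionnaires): "The first SAQ questionnaire will be administered before the staged revascularization, i.e., ~4 weeks after the ACS event". The questionnaire is repeated at 3 and 12 months.
- **SAQ hypothesis** (Hypothesis): the arms are compared on 3-month change in the summary score, the reference arm being defined as "B = Change in the SAQSS after 3 months to baseline with reference treatment". The error rate is two-sided 5%, the power 90% and the stated sample size 178. Study Endpoints lists this change as secondary.

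**The concern.** A linear regression fits a continuous outcome, and the SAQ scores are the obvious candidate. For them the natural covariate is the patient's own earlier score. The protocol collects it and builds the hypothesis on change from it, but does not make it a candidate. The scale stops at 100, and the Power Calculation section cites a study in which SAQ rose from about 82 to about 98. The room to improve therefore depends on where a patient starts.

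Two further weaknesses come from the same sentences. The covariates are picked by the trial's own outcome data, so the adjusted model is unknown until the data are seen. And because no outcome is named, a reader cannot tell which result the regression is meant to support.

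At stake is precision in the SAQ comparison, and how far the adjusted SAQ result counts as pre-specified.

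**Working it through.** **1. The plan's own SAQ sample sizes.** For two means, n per arm = 2(1.960+1.282)²(SD/Δ)².

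- 98 against 86 with SD 21 (Power Calculation): Δ = 12 gives 65 per arm, or 130, as stated.
- The 178 in the Hypothesis section cannot be reproduced, because no difference or SD stands beside it. The other SAQ figures in the article give, at 90% power, 136 (14 points, SD 25), 160 (14 points, SDs 24 and 30), 194 (14 points, SD 30) and 230 (11 points, SDs 28 and 23). Read backwards, 178 implies a standardized difference of 3.242 × √(2/89) = 0.486.

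**2. ANCOVA against an unadjusted change score.** Let s₀ and s₁ be the baseline and follow-up SDs and r their correlation.

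- Var(change) = s₀² + s₁² − 2r·s₀s₁
- Var(ANCOVA) = s₁²(1 − r²)
- Difference = (s₀ − r·s₁)², which is never negative

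With s₀ = s₁ = s these become 2s²(1−r) and s²(1−r²), and the ratio is (1+r)/2.

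The article gives no r, so it is an assumption, ranged from 0.3 to 0.7. If 178 was sized on the change score, the N needed is 2 × ⌈89(1+r)/2⌉, and the power at 178 is Φ(3.242/√((1+r)/2) − 1.960).

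| Assumed r | Variance ratio | N instead of 178 | Power at 178 (planned 90%) |
|---|---|---|---|
| 0.3 | 0.65 | 116 | 98.0% |
| 0.4 | 0.70 | 126 | 97.2% |
| 0.5 | 0.75 | 134 | 96.3% |
| 0.6 | 0.80 | 144 | 95.2% |
| 0.7 | 0.85 | 152 | 94.0% |

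**3. What the stepwise rule does to the treatment test.** The simulation had 200 patients, no treatment effect, r = 0.5, treatment forced in, nine independent noise covariates, the stated entry and stay thresholds, and 4,000 runs. The Monte Carlo SE of a 5% error rate is √(0.05×0.95/4000), about 0.35 points.

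| Analysis | Type I error | SD of treatment estimate |
|---|---|---|
| Change score, stepwise | 5.4% | 0.1416 |
| Change score, unadjusted | 5.0% | 0.1402 |
| ANCOVA on baseline | 5.1% | 0.1226 |

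The mean model SE under stepwise selection was 0.1405, against an actual SD of 0.1416, so the intervals were not materially too narrow. The variance ratio of ANCOVA to the unadjusted change score was 0.76, against 0.75 in theory. In this setting the stepwise search gained no precision, while the omitted baseline would have.

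**4. The binary primaries.** Both stated sample sizes of 176 reproduce with the unpooled two-proportion formula (33% against 13% at 90% power; 14.8% against 32.4% at 80%). ANCOVA on SAQ does not touch them.

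**The case against.** **The regression is nowhere assigned to the binary primaries.** A reader might infer that a linear model will be fitted to a 0/1 endpoint. The text does not support that: both primaries have their own suitable methods. What stands is only that the regression's outcome is unnamed.

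**Stepwise selection is not shown to invalidate the test.** A reader might infer intervals that are too narrow or excess false positives. Treatment is forced in, and the simulation shows no material inflation. Its covariates were independent noise, so it does not cover every case, but it gives no ground for a claim of invalidity. What stands is that the model is chosen from the data.

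**The Hypothesis section defines a quantity and prescribes no test.** This is correct. ANCOVA on change, with baseline as covariate, gives the same treatment estimate as ANCOVA on the follow-up score, so that section need not be rewritten. An SAP might also hold the SAQ model. But the article does not leave the matter open: it states a selection rule and a covariate list, and baseline SAQ is not on the list.

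**SAQ change is secondary and exploratory.** This stands and limits the weight of the point. The 90%-power hypothesis on it sits uneasily with that status; the two sections need reconciling, but that is a separate matter.

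**Equal variances are doubtful near a ceiling.** This affects the size of the gain but not its direction, since the difference (s₀ − r·s₁)² cannot be negative. Linear ANCOVA does not remove the ceiling.

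**The baseline appears to follow randomization.** Consent and Randomization places allocation after the index procedure and QFR measurement, and the first SAQ comes about 4 weeks after the ACS. Blinding helps ("The participants and treating physicians will be blinded to the treatment group allocation"), but patients may know whether a staged procedure is scheduled. This is a real caveat, but it does not favour the current plan. A change score subtracts the whole of any arm difference in that first SAQ; ANCOVA subtracts only the fraction given by the regression slope, which is r under equal variances.

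**Conclusion.** The point holds as a modest, inexpensive improvement to the SAQ analysis. The protocol fixes a data-driven linear model without naming its outcome and leaves out the covariate that matters most to the SAQ hypothesis it states. ANCOVA would cut the variance of the SAQ comparison by 35% to 15% relative to an unadjusted change score. This assumes a correlation of 0.3 to 0.7, equal variances, and that the first SAQ is the baseline meant in the Hypothesis section. The N and power columns above also assume that 178 was sized on change, which the article does not say.

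The gain does not extend to either primary endpoint and does not alter the trial's sample size. The case against the stepwise rule is that it forgoes available precision and lets the data choose the model; an inflated type I error is not part of it.

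**What to change.** 1. Delete the stepwise rule and name the outcome of every regression.
2. Analyse the 3- and 12-month SAQ summary and domain scores by ANCOVA: follow-up score on arm, the first SAQ score, and a short fixed covariate list drawn from those already named (for example ACS type, age, sex and diabetes).
3. Leave the binary primaries on their stated difference in proportions and relative risk. If an adjusted analysis of them is intended, use a binary model with fixed covariates, and do not require baseline SAQ in it. Requiring it would drop patients without a first SAQ from a complete-case model.
4. State that the first SAQ is the baseline, when it is taken relative to randomization, and why allocation is not expected to have affected it by then.

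**Cost:** wording, settled before outcomes are seen by arm; no new data and no change in sample size. Patients without a first SAQ drop out of the SAQ model, as they already would from the change score.

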**Methods and Analysis:**

After treatment of the culprit lesion(s), a total of 200 consecutive ACS patients will be randomized 1:1 to angiography- vs. QFR-guided revascularization of non-culprit stenoses. Patients and clinicians responsible are blinded to the randomization group. The primary functional endpoint is defined as the proportion of patients assigned to medical treatment in the two groups. The primary clinical endpoint is a composite of death, non-fatal myocardial infarction, revascularization and significant angina at 12 months. Secondary endpoints include changes in the SAQ subgroups, and clinical events at 3- and 12-month follow-up.

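### Two primary endpoints are each sized and judged at the full two-sided 5%, with no testing order, alpha split or rule for what counts as success

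*Protocol article*

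**What the plan says.** The abstract (Methods and Analysis) and Study Endpoints both list two primary endpoints:

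- Functional: "The primary functional endpoint is defined as the proportion of patients assigned to medical treatment in the two groups".
- Clinical: "The primary clinical endpoint is a composite of death, non-fatal myocardial infarction, revascularization and significant angina at 12 months". Study Endpoints adds unplanned hospitalization for angina or heart failure and specifies the angina component as SAQ below 90.

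Power Calculation sizes each on its own. For the functional endpoint, "176 patients are required to have a 90% chance of detecting, as significant at the 5% level" a difference "from 33% in the QFR group to 13% in the angiography group". For the clinical endpoint, "176 patients are required for a power of 80% and an alpha error of 5" per cent, with 14.8% expected in the QFR group and 32.4% in the angiography group.

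Statistical Analysis of Primary and Secondary Endpoints gives one criterion for all tests, a p-"value <0.05 (2-sided) will be considered statistically significant", and downgrades only the secondary endpoints to exploratory p-values. Binary outcomes are to be compared as proportions with exact methods. The same section adds that "time to events within 12 months will be compared between groups using log-rank tests".

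The Hypothesis section states an "Overall type I error rate = 5% (two-sided) with a power = 90" per cent. This stands beside the null hypothesis on 3-month change in the SAQ summary score.

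**The concern.** With two primaries and no rule linking them, either one reaching p<0.05 can be reported as a positive primary result. That gives two chances of a false positive at 5% each.

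The two endpoints also mean different things. The arms apply different decision rules to non-culprit lesions, so a difference in the share assigned to medical treatment is what the design expects (33% against 13%). It is not evidence of the benefit in the study hypothesis under Study Design, which is fewer events and less angina. Without a success rule, a trial that changes decisions but not outcomes could be presented as having met its primary endpoint.

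The text does not settle which endpoint decides. Power Calculation refers to the functional endpoint as the primary outcome measure. The limitations paragraph of the Discussion places the primary endpoint at 12 months, and the mITT definition under Statistics relies on a 12-month assessment; both point to the clinical composite. The only formal null hypothesis concerns a third quantity, the 3-month SAQ summary score.

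**Working it through.** **1. Was an alpha split built into the sample size?** Inputs are from Power Calculation, with 1:1 allocation. The formula is the two-proportion normal approximation with unpooled variance:

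n per arm = (z₁₋α/₂ + z_power)² × [p₁(1−p₁) + p₂(1−p₂)] / (p₁−p₂)²

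- Functional, α = 0.05, power 90%: (1.960 + 1.282)² × (0.2211 + 0.1131) / 0.20² = 10.507 × 8.355 = 87.8, so 88 per arm and 176 in total.
- Clinical, α = 0.05, power 80%: (1.960 + 0.842)² × (0.2190 + 0.1261) / 0.176² = 7.849 × 11.14 = 87.4, so 88 per arm and 176 in total.

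Both stated totals are reproduced exactly at undivided alpha. At α = 0.025 the same formula gives 208 and 212. No split was built in.

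**2. Error rate when both nulls are true.**

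- Independent tests: 1 − 0.95² = 9.75%.
- Any dependence: at most 0.05 + 0.05 = 10%.

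A null simulation (20,000 runs, 100 per arm, assumed null rates 23% functional and 23.6% clinical, exponential event times, independent endpoints) gave 9.7% for the functional or clinical proportion test.

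**3. Does the log-rank matter?** Suppose it were a second test of the clinical composite. In the same simulation:

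- clinical proportion test alone 5.2%; by either method 5.5%;
- any of the three tests 10.0%, against 9.7% without the log-rank.

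It adds about 0.3 to 0.5 percentage points. Nearly all the inflation comes from having two primaries.

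**4. Error rate when the functional endpoint truly differs.** Only the clinical null can then be falsely rejected, so the error is about 5% (5.5% if both methods counted).

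**5. Power at the planned 100 per arm** (pooled variance under the null, everyone evaluable):

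z = [|p₁−p₂|√n − 1.960 √(2p̄(1−p̄))] / √(p₁(1−p₁)+p₂(1−p₂))

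- Functional, p̄ = 0.23: (2.000 − 1.960 × 0.595) / 0.578 = 1.44, power 92.5%.
- Clinical, p̄ = 0.236: (1.760 − 1.960 × 0.601) / 0.587 = 0.99, power 84.0%.
- Both, if independent: 0.925 × 0.840 = 78%.
- With 0.025 for each endpoint instead: 87.5% and 76.0%.

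**6. Sensitivity.** If the functional rates were 25% and 13% (an assumption, not in the article), functional power would be about 58%, and the chance of passing both steps about 0.58 × 0.84 = 49%.

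**The case against.** The strongest reply is that the article condenses a fuller protocol, that a testing order is commonly set in an analysis plan that is not shown, and that the abstract numbers two separate aims. Part of this stands: an unseen plan may contain the rule. But the article is not silent. It fixes two primaries, full alpha for each and one threshold, and it sets only the secondary endpoints apart as exploratory. A numbered list of aims is not a testing sequence.

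A second reply is that the 9.75% needs both nulls to be true, which is unlikely if different decision rules almost guarantee a functional difference. This stands, and it limits the figure. What then remains is the undefined success rule.

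Four stronger readings are tempting, and the document does not support them:

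- **That the article breaks its own promise of 5% overall.** The phrase is attached to 3-month change in SAQ summary score, which Study Endpoints lists as secondary. It is not an express promise across the two primaries.
- **That the error reaches 14.3%** (1 − 0.95³). This counts the SAQ summary score as a third confirmatory test, although secondary endpoints are declared exploratory.
- **That the clinical endpoint has two competing primary tests.** The log-rank clause speaks of time to events and does not name the composite. The sizing as two proportions and the 12-month definition both point to the proportion test.
- **That most event times in the composite would be visit dates.** SAQ below 90 can indeed be seen only at scheduled assessments, but the article gives no expected split between SAQ-defined and dated events.

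**Conclusion.** The point holds in a limited form. As written, two primary endpoints are each tested at two-sided 5% with no rule connecting them. The family-wise error is 9.75% if both nulls hold and the tests are independent, with an upper bound of 10% under any dependence. If the functional endpoint truly differs, the clinical error stays near 5%, and the harm is that functional success could be presented as success of the trial.

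Requiring both endpoints to succeed would also hold the error at or below 5%, but the article does not say this. The Hypothesis section needs reconciling with Study Endpoints, because its overall 5% belongs to a secondary endpoint.

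The power figures rest on the article's assumed rates, 100 evaluable patients per arm and independence of the two endpoints. Missing 12-month assessments would lower them.

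**What to change.** Before any unblinded analysis, state the following:

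- **Order.** Fixed sequence at two-sided 5%: first the functional endpoint; only if it is significant, the 12-month clinical composite.
- **Deciding test.** The comparison of 12-month proportions is the only primary test of the clinical composite.
- **Success claim.** A claim of improved outcomes requires the clinical endpoint to succeed. Functional success alone shows only that treatment decisions changed. The ordering does not prevent over-claiming without this sentence.
- **Secondary endpoints.** The SAQ summary score and the others stay exploratory, and the overall type I error statement moves from the SAQ hypothesis to the primary endpoints.
- **Log-rank.** Supportive only, on dated clinical events (death, myocardial infarction, unplanned revascularization, unplanned hospitalization).

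The cost is wording plus some power for the clinical endpoint: 78% to pass both steps against 84% alone at the assumed rates, and about 49% in the smaller-difference example above. A Bonferroni split is the alternative. It keeps the clinical test independent of the functional result, at 76.0% power with 100 per arm, but keeping the stated power of 90% and 80% would need 208 and 212 patients by the article's own formula, above the planned 200.
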